Once a telephone or email inquiry or referral from a partnering organization is received, project staff will call the family to explain the purpose and procedures of the study. If the participant indicates interest in participation, project staff schedule an assessment appointment with the family. The potential participant will complete a screening assessment consent form, which will allow the assessor (principal investigator [PI] for English, bilingual research assistant for Spanish) to administer the Modified Checklist for Autism in Toddlers, Revised, with Follow-Up (MCHAT), which is a parent-report screening tool to assess autism risk [27]. If the child scores below 3 on the MCHAT or does not meet all eligibility requirements, the parent will be compensated for the visit (US $25) and receive an assessment report, and all study materials will be destroyed. The assessor will continue with baseline assessments if the child and family meet all eligibility criteria: child is between 16 and 36 months of age, is minimally verbal or pre-verbal, scores 3 or above on the MCHAT, and has no other physical or sensory disabilities.

Before starting baseline assessments, the assessor will review the informed consent form in the appropriate language with the participant, and any questions will be answered. The participant will be told that this is a research study, that his or her participation will not positively or negatively affect the provision of services to the family, and that he or she is free to decline to answer any questions or to cease participation at any point. The confidentiality of the information will be assured. The participant will be told that no identifying information will be retained on any of the data collection forms and that a unique and nonidentifying ID code number will be assigned in lieu of his or her name. The participant will be asked to sign 2 copies of the informed consent (1 for the participant to keep, 1 for the project files), after which baseline assessment will begin. Participants will then receive 6 weekly links to the online

modules in their language of preference as outlined in the following sections.

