### Control Measures

#### Demographic Questionnaire

The demographic questionnaire will be created by investigators. The questionnaire will include questions regarding parent age, education, income, employment, English language proficiency, health status, child age, and gender. It will be collected pre-intervention.

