### Quantitative Analysis

Linear mixed-effects model analysis will be used to explore most parent-reported and coded outcomes because (1) it allows for individual differences in parent responses over time to be included in the model as a random effect so that the variance in responses is partitioned into a time-within-parent component and a between-parent component, (2) using maximum likelihood estimation in a linear mixed-effects model allows for the use of all available data to evaluate the parameter values and is currently considered the state-of-the-art method for handling missing data, and (3) linear mixed-effects models perform well with small samples. The linear mixed-effects models will evaluate time as the main fixed effect using discrete time variables (ie, 2 dummy variables with baseline as the “referent”). Separate regression models will be run for each outcome. Additional variables to be included in each regression model will include total score of other services used, recruitment site, and only demographic variables significantly related to the outcome (given the small sample size).

Cohen d effect sizes will be calculated between time periods and reported for all analyses of interest as a measure of the magnitude of any changes in outcome measures. Mixed models will also be utilized to test if changes from baseline on outcome variables differ by parent language preference for training (Spanish or English) over time. HOLA acceptability will be determined by the average parent rating on the Parent Satisfaction measure. If the average ratings for parent satisfaction items are 3.5 or higher, the training may remain as written. Items with parent satisfaction ratings lower than 3.5 will be explored during Spanish and English focus groups, and individual items will be refined according to feedback. Focus group transcripts will be coded and analyzed thematically to inform continued program improvement.

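### Maximum likelihood covers missing outcomes, not missing covariates: under a standard fit, one declined demographic item can remove a whole dyad from a primary model while adding almost nothing to the time estimate

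*Protocol article*

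**What the plan says.** In the protocol article, Quantitative Analysis gives three reasons for linear mixed-effects models. The second is that maximum likelihood "allows for the use of all available data to evaluate the parameter values"; the article also describes it as the best current approach to missing data. Time enters as two dummy variables with baseline as the reference, and each outcome has its own model.

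The covariate rule comes in the same paragraph: "Additional variables to be included in each regression model will include total score of other services used, recruitment site, and only demographic variables significantly related". The relation meant is with the outcome being modelled.

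Three other sections determine how those covariates behave:

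- **Demographic Questionnaire:** the items are "parent age, education, income, employment, English language proficiency, health status, child age, and gender. It will be collected pre-intervention". This is the only collection, so each item is constant over a dyad's visits.
- **Service Use Questionnaire:** the services score is collected before the intervention, after it and at follow-up, so it varies over time.
- **Recruitment and Consent Procedures:** each parent is told that "he or she is free to decline to answer any questions".

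**The concern.** A mixed-model likelihood, as standard software fits it, is conditional on the covariates. A dyad with a missed outcome visit contributes its other visits, but a row with a missing covariate is deleted. Because a demographic item has one value per dyad, one unanswered item deletes every row of that dyad in any model containing it.

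The screen is applied outcome by outcome. Social communication, parent fidelity and child development knowledge are the primary outcomes measured at three visits. Each could carry a different set of demographics and so be analysed on a different subset of the 24 dyads. Each subset would be selected by willingness to answer items such as income, employment or health status. In a trial meant to inform work with underserved families, that selection matters at least as much as the lost precision.

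The loss brings little in return. A covariate that does not change over time cancels from a within-dyad change.

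**Working it through.** **1. The plan's own figures.** Inputs from Sample Size Determination: effect size 0.8 between baseline and postintervention, α .05 (two-sided assumed), 80% power, n = 13, and 97% power at 24 dyads.

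- Normal approximation for a paired change: n = ((1.960 + 0.842)/0.8)² = 12.26, rounded up to 13.
- Power at n = 24: 97.5% by the normal approximation, 96.3% by the noncentral t.

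The stated figures reproduce to within rounding or approximation. The noncentral t is used below, so the reference is 96.3%.

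**2. Why a time-constant covariate leaves the contrast alone.** Write y(i,t) = time(t) + β·x(i) + b(i) + e(i,t), with x the demographic item and b the dyad's random intercept. The change from baseline is y(i,1) − y(i,0) = time(1) − time(0) + e(i,1) − e(i,0). Both x and b cancel. With complete visits, the time coefficient and its standard error do not depend on whether x is in the model as a main effect.

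**3. Numerical check.** One simulated set of 24 dyads × 3 visits was fitted by maximum likelihood with a random intercept. It illustrates the mechanism only; the shifts are not estimates for this trial.

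| Model and data | Records | Dyads | Baseline-to-post effect | SE |
|---|---|---|---|---|
| Time only, complete | 72 | 24 | 0.633 | 0.146 |
| + income + site, complete | 72 | 24 | 0.633 | 0.146 |
| + income + site, income missing in 4 dyads | 60 | 20 | 0.563 | 0.153 |
| + income + site + services score, complete | 72 | 24 | 0.582 | 0.153 |

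Two further results mark the limits:

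- A services score missing at one visit in 4 dyads left 68 records and all 24 dyads, so it costs a record and not a dyad.
- With both post-baseline outcomes missing in 5 dyads (62 records), adding income moved the time effect from 0.620 to 0.626. Baseline covariates then do some work, but little.

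**4. Size of the loss.** The article gives no decline rate, so the rates here are assumptions. With k selected items, each declined independently at rate p, the expected number of dyads kept is 24 × (1 − p)^k. Example: 24 × 0.90² = 19.4. Power is for a paired t test at 0.8, two-sided .05.

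| Items in model | p = 2% | p = 10% | p = 20% |
|---|---|---|---|
| 1 | 23.5 kept, 96.0% | 21.6 kept, 94.3% | 19.2 kept, 91.2% |
| 2 | 23.0 kept, 95.6% | 19.4 kept, 91.6% | 15.4 kept, 83.2% |
| 3 | 22.6 kept, 95.2% | 17.5 kept, 88.2% | 12.3 kept, 72.6% |

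Confidence interval width is proportional to t(.975, n − 1)/√n. For n = 24 this is 2.069/4.899 = 0.422; for n = 19 it is 2.101/4.359 = 0.482. The ratio is 1.14, so the interval is about 14% wider.

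**5. Selection, as an illustration.** Suppose the 20% who decline gain 0.5 SD less than the rest, who gain m. The mean over all dyads is 0.8m + 0.2(m − 0.5) = m − 0.10, but the model that drops decliners estimates m, which is 0.10 SD too high. Both inputs are assumptions, and the direction could be the reverse.

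**The case against.** The case for leaving the text alone has real force, and several stronger conclusions that a reader might draw are not supported.

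- **That all the planned covariates are useless for the time effect.** This is wrong for the services score. It is measured at each visit, can change the time effect, and is the plan's adjustment for concurrent therapy in a single-group design. Recruitment site should be known to staff from the referral route, and child age is needed for eligibility, so neither is likely to be lost to a declined question.
- **That the plan lacks a procedure for missing covariates.** That detail commonly sits in an analysis plan, and none is shown. Deletion is a software default, and imputation or a joint likelihood would be compatible with the text. What can be criticised is what the article does state: maximum likelihood as the answer to missing data, next to a covariate rule for which it is not the answer.
- **That high refusal should be expected.** The Introduction's remarks on the immigration climate concern seeking services, not skipping items after consent. The right to decline is routine consent wording. The article also describes measures to build trust.
- **That the trial is underpowered or biased as a result.** With one or two items at 10%, power stays above 90%, and loss occurs only if a declined item passes the screen. The article calls these analyses exploratory and looks to later randomised trials for robust evidence.

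What remains is that the stated rule can discard whole dyads, outcome by outcome, for a gain in the time estimate that is nil with complete visits and slight otherwise.

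**Conclusion.** The point holds for the parent-reported, once-collected demographics that enter through the significance screen. For them, the stated rationale claims more than a standard fit delivers. It does not extend to the services score, and it leaves the sample-size figures unaffected.

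The likely size is modest. From a reference of about 96%, power at effect size 0.8 falls to about 94% (one item) or 92% (two items) at an assumed 10% decline rate, and to about 91% with one item at 20%. Only heavier assumptions, such as three items at 20%, take it below 80%. These figures assume independent skips, complete outcome visits and row deletion. The change is still worth making, because the analysed families could otherwise differ between primary outcomes for reasons unrelated to the intervention, and avoiding this needs only wording.

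**What to change.** In Quantitative Analysis:

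1. Reword the missing-data reason to say that likelihood estimation uses all observed outcome records, so that dyads with a missed visit are retained, and that it does not by itself handle missing covariates.
2. For each modelled outcome, fit the primary time model to all enrolled dyads without significance-screened demographics. Keep the services score as the plan specifies, or report the model with and without it. Site can stay, since it should be complete.
3. Put demographics in a supportive model, with missing baseline items handled by simple imputation or a missing category so that no dyad is dropped.
4. Report the number of dyads and records in each model.

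The cost is analysis wording only. When visits and covariates are complete, removing time-constant demographics leaves the time estimate unchanged. The downside is that, when visits are missing, the primary model loses the little that demographics say about them; the supportive model shows whether that matters.

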## Methods

### Objectives and Study Design

This pilot study will utilize a single-group, pilot, pre-post design with follow-up assessments 6 weeks later. All assessments described in the subsequent paragraphs are available in English and Spanish. It is hypothesized that the HOLA parent training will improve parent knowledge of ASD and child development, increase fidelity of implementation of the strategies taught, and improve child social communication. Additionally, we predict that the parent will experience gains in empowerment and reductions in parenting stress, and the children will have reductions in challenging behavior and display improved social skills. Finally, we predict that there will be no difference in participant outcomes between Spanish and English language trainings.

To test the HOLA intervention, we will recruit 24 Latinx toddler-parent dyads (16-36 months old) with elevated risk for ASD from the East and South Los Angeles regions to measure the effects of the HOLA intervention on parent knowledge of child development, parent PRT fidelity of implementation, and child social communication. We will also measure parent satisfaction with the intervention and explore the impact of HOLA on parent stress, family empowerment, and child behavior. Additionally, because participants will choose whether they would prefer to receive the intervention in Spanish or English, we will assess whether language has an impact on effectiveness of and satisfaction with HOLA.

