### Enrollment and Participation

Over 1 year, 24 parent/child dyads will participate in the study. The parents will receive 6 weekly emails or text messages, each with an active link to access an online training module. All electronic data will be stored in a password-protected university server, and only IRB-authorized personnel will be granted password access.

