#### Satisfaction

Parents will complete a survey rating their satisfaction with their training on a 5-point Likert scale. Items will include, but are not limited to, accessibility, helpfulness, convenience, and thoroughness of training program and materials. Space for parent suggestions will also be provided. This will be collected postintervention.

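### The 3.5 acceptability rule uses one average parent rating with no split by language, so a version or item rated below 3.5 in one language can pass it

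*Protocol article*

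**What the plan says.** Satisfaction is listed under Primary Outcome Measures. On the instrument: "Parents will complete a survey rating their satisfaction with their training on a 5-point Likert scale". On timing: "This will be collected postintervention".

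The decision rule is in Quantitative Analysis and has three parts:

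- Overall criterion: "HOLA acceptability will be determined by the average parent rating on the Parent Satisfaction measure".
- Consequence of passing: "If the average ratings for parent satisfaction items are 3.5 or higher, the training may remain as written".
- Item trigger: "Items with parent satisfaction ratings lower than 3.5 will be explored during Spanish and English focus groups". Flagged items are then refined according to the feedback.

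On language, Objectives and Study Design explains that the comparison arises "because participants will choose whether they would prefer to receive the intervention in Spanish or English", and commits that "we will assess whether language has an impact on effectiveness of and satisfaction with HOLA". The same section predicts no difference in outcomes between the two trainings. The one language analysis in Quantitative Analysis is a mixed model that asks whether change since baseline differs by training language.

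Qualitative Analysis adds focus groups drawn from a subsample of Spanish-speaking and English-speaking parents. Satisfaction is a topic in them whatever the ratings show.

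**The concern.** HOLA is delivered in two language versions, and each parent uses one. A single average over all parents answers whether the mix of users who happened to enrol was satisfied. It does not answer whether each version is acceptable. A well-liked version can lift a poorly rated one over the threshold, and the same holds for a single item that works in one language and not in the other.

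The article commits to looking at satisfaction by language, but the analysis it describes cannot do so: satisfaction has no baseline value, hence no change to model. Nor does any language result enter the rule. At stake is the keep-or-revise decision on a primary outcome of a study built on a bilingual premise.

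**Working it through.** **No stated figure to reproduce.** The article gives no operating characteristics for the 3.5 rule. Its sample size and power figures concern the pre-post comparison and have no bearing here.

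**Inputs from the article.** Threshold 3.5 on a 5-point scale; 24 dyads ("Over 1 year, 24 parent/child dyads will participate in the study"); language chosen by the parent, split not given.

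**Assumptions.** The split, the language means and a rating SD of 1.0 within language. None is in the article, so a range is shown.

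**Step 1. How low can one language fall while the pooled mean still reaches 3.5?** With n_F raters in the low-rated language and n_O in the other, at mean m_O, the lowest passing mean is (24 × 3.5 − n_O × m_O) / n_F, bounded below at 1. For 12 and 12 with m_O = 4.0: (84 − 48) / 12 = 3.00.

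| Low-rated / other raters | m_O = 4.0 | m_O = 4.5 | m_O = 5.0 |
|---|---|---|---|
| 6 / 18 | 2.00 | 1.00 | 1.00 |
| 8 / 16 | 2.50 | 1.50 | 1.00 |
| 12 / 12 | 3.00 | 2.50 | 2.00 |
| 16 / 8 | 3.25 | 3.00 | 2.75 |

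**Step 2. How often would the rule pass?** Take true means of 4.2 (English) and 3.0 (Spanish). The pooled mean is (n_E × 4.2 + n_S × 3.0) / 24 with standard error 1/√24 = 0.204. The Spanish mean has standard error 1/√n_S. The pass probability is Φ((mean − 3.5) / SE).

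| English / Spanish | Pooled mean | Pooled passes | Spanish SE | Spanish alone passes |
|---|---|---|---|---|
| 16 / 8 | 3.80 | Φ(1.47) = 93% | 0.354 | Φ(−1.41) = 8% |
| 12 / 12 | 3.60 | Φ(0.49) = 69% | 0.289 | Φ(−1.73) = 4% |
| 8 / 16 | 3.40 | Φ(−0.49) = 31% | 0.250 | Φ(−2.00) = 2% |

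**Step 3. Cross-check with whole-number ratings.** A simulation of one item with ratings rounded and limited to 1–5 (100,000 replicates; resulting means about 3.0 and 4.1) counted how often the pooled mean reached 3.5 while the low-rated group's observed mean was below it. This happened in 80% of replicates with 8 low-rated and 16 other raters, 58% at 12 and 12, and 25% at 16 and 8. Moving the low mean between 2.8 and 3.2 gave 70–80%, 43–62% and 11–40%.

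**Step 4. Does the described language analysis cover satisfaction?** It tests differences in change since baseline. Satisfaction is collected once, after the intervention, so it has no such change.

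**The case against.** Several points on the other side are fair.

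- **Pooling is inferred.** The article never says that ratings are combined across languages, and a condensed article may leave tabulation by language to a fuller document. But the rule, its threshold and its consequence are all stated here, and the neighbouring sentence on mixed models names the languages where this one does not.
- **The focus groups are a second route.** A reader might infer that an item weak in only one language would never come to light. The article does not support that. The groups include parents of both languages, discuss satisfaction regardless of the ratings and feed into revisions, and the survey leaves space for suggestions. What remains is narrower: the groups are a subsample with a flexible protocol, and the item-by-item exploration is triggered only by a rating below 3.5.
- **The rule is permissive.** It says the training may stay as it is. It does not oblige the investigator to keep a version shown by other means to be weak.
- **Power.** A reader might infer that a language comparison with 24 parents would miss the problem. For a 0.8 SD gap, a two-sample t test has 42% power at 16 and 8. The gap in Step 2, however, is 4.2 − 3.0 = 1.2 SD, where power at that split is about 75%. Low power is therefore not the argument. The point is that the analysis described does not fit satisfaction and that no language result enters the rule.
- **The size depends on the split.** Masking is strong when the low-rated version has equal or fewer users and weaker when it has the majority. Nothing in the article says which language will be the smaller group or the lower-rated one; Spanish serves here only as the example.

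**Conclusion.** The concern holds in this limited form. As naturally read, the numeric rule can pass a version or an item that one language group rates below 3.5, and the described language analysis cannot serve the stated aim of comparing satisfaction by language.

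For a true gap of 1.2 points and an SD of 1.0, the chance that the pooled rule passes runs from 31% to 93% across the three splits shown, against 2% to 8% for the low-rated group judged alone. These figures rest on assumed means, SD and splits. That masking is possible does not: at 12 and 12, language means of 3.0 and 4.0 pool to exactly 3.5 and pass.

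The documents do not show that a weak version would go unnoticed or would have to be kept. This is an inexpensive repair to a stated rule on a primary outcome, and worth making.

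**What to change.** State in Quantitative Analysis that the 3.5 threshold is applied within each language version, both to the overall average and item by item, and report the number of raters per language. Send any item below 3.5 in either language to that language's focus group. Give the pooled mean as description only. Replace the change-based model, for satisfaction, with a comparison of postintervention ratings by language.

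This takes a sentence or two, needs no new data and uses focus groups already planned. The cost is more false flags. With an SD of 1.0, an item with a true mean of 3.8 falls below 3.5 with probability Φ(−0.3/0.354) = 20% among 8 raters, against Φ(−0.3/0.204) = 7% among 24. If the true mean is 3.8 in both languages, at least one group flags the item with probability 1 − 0.80 × 0.88 = about 29% at 8 and 16 (16 raters: Φ(0.3/0.25) = 0.88), or 1 − 0.85² = about 28% at 12 and 12 (Φ(0.3/0.289) = 0.85). The consequence of a false flag is one more item for discussion. If that load is a worry, the number of raters shown beside each average lets the team weigh a marginal result.
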